### Intervention Description

#### Overview

The site randomized to pathway 1 for the first period nominated ≥2 primary care clinicians and *kaiāwhina* to be trained by qualified members of the research team in the operation and daily quality audit of the Cepheid GeneXpert IV instrument. POC training was overseen by the research team’s molecular scientist in the week before recruitment began. This consisted of orientation and familiarization runs using contrived samples and official training directly from Cepheid via a video link. The technology is robust, but user training and support are vital. Only those holding a training certificate issued by Cepheid are authorized to run patient samples. Regular in-person, on-site POC updates run throughout the trial. User and instrument proficiency testing is built into the implementation process and conforms to the New Zealand Best Practice Guidelines for Point-of-Care Testing [32]. In addition, the research team and site clinicians involved in POC testing are participants in the Royal College of Pathologists of Australasia Quality Assurance Program [33]. The Cepheid GeneXpert IV instruments used in this study are loaned from the Australian Centre for the Prevention of Cervical Cancer.

A 2- to 4-week washout took place between the 2 study periods. The second site received the same training schedule on how to use the Cepheid GeneXpert IV instrument, and the instruments were transported, set up, and tested at the second study site.

#### Pathway 1

Following self-collection, the vaginal sample is processed onsite by the Cepheid GeneXpert IV instrument, taking approximately 1 hour, and the result is documented in the patient management system (PMS). The intention is for women to receive the HPV test result in person onsite, as soon as the test result is available.

Women with hrHPV-positive results receive immediate on-site information about the result, its significance, the next steps, and support. An appointment for colposcopy is made straight away by a phone call to the appointment clerk at the hospital. This phone call is followed up with a referral letter from the referring primary care clinician.

Women with hrHPV-negative results are informed of the result and its significance and advised that they will not need screening for 5 years.

If a woman is unable to stay for an hour to receive her test result, her contact details are taken, and she is contacted as soon as the result is available.

#### Pathway 2

Following vaginal sample self-collection, the woman is asked how she would prefer to receive the result (by SMS text messaging, phone, or in person). The sample is then transported at room temperature to the diagnostic laboratory as part of the practice’s routine laboratory collection. hrHPV genotyping is performed using the Roche Cobas 4800 system. This system detects 14 hrHPV types (16, 18, 31, 33, 35, 39, 45, 51, 52, 56, 58, 59, 66, and 68) and provides a result which distinguishes types 16 and 18 from “other” high-risk types [34]. The use of dry vaginal swabs has been validated in international published studies, and the laboratory is undertaking this testing “off-label” [35,36]. The samples are disposed of in line with the standard pathology laboratory procedures. Test results are sent electronically (encrypted as other routine results) to the ordering primary care clinician and entered into the PMS, as cytology results would be.

Women with hrHPV-positive results are informed of the result and its significance by phone or in person. Information regarding the next steps and support are provided. The primary care clinician sends a referral letter to the colposcopy service at the hospital. The woman is triaged for a colposcopy appointment, and the appointment time is sent to the woman by mail, with or without phone follow-up.

Women with hrHPV-negative results are informed of the result and its significance and advised that they will not need screening for 5 years.

### Data Collection and Analysis

Regular 3 monthly visits to the research sites are made by the members of the research team. These visits include updating the clinic staff on any amendments and audits of the PMS to ensure that the results are documented accurately and coded, given to women, and followed up appropriately. The research team’s molecular scientist visits regularly to audit the POC instruments and sample testing process compliance. The practices have ownership of their data and all the results. Researchers are readily available via phone and email to support practices.

The ordering clinician and practices have the primary responsibility for follow-up. For clinical safety, the unblinded study statistician checks for colposcopy referrals and attendance. This is checked no sooner than 3 months from the hrHPV test date, so the primary outcome is not influenced but ensures that practices can contact any woman who has not yet attended a colposcopy appointment.

Follow-up colposcopy and treatment performed within the public health service are free for Aotearoa citizens and permanent residents. The new NCSP will start in September 2023, and the women in this trial will be registered with the new program appropriately.

Data collection and management are conducted as follows: copies of consent forms, POC test results, and laboratory results are provided to the research team by the study sites and used to track recruitment and monitor safety. Every 6 months, the colposcopy services provide data to the study statisticians: colposcopy attendance and date, colposcopy assessment and outcome, cytology result (if any) at colposcopy, histology, treatment plan, and any treatment provided. No other research team members have access to colposcopy data.

Each person using a health or disability support service in Aotearoa has a unique National Health Index (NHI) number [37]. The research team provides the NHI numbers of the participating women to the National Screening Unit to obtain cervical screening and clinical history at the start of the study period from the NCSP. The NHI number is also used to obtain ethnicity, the deprivation index (socioeconomic status), and age from the NHI data set.

The NHI number is replaced with a unique study code in all research data sets for analysis. No individuals will be identifiable in the reporting of study findings.

Study-specific source documents are maintained in locked file cabinets in locked rooms of Te Tātai Hauora o Hine, Victoria University, Wellington. Electronic data are stored on the secure Victoria University of Wellington server in restricted access folders and password-protected files. The data will be retained for 10 years and then destroyed securely.

Qualitative data collection is conducted as follows: up to 40 women who screen and test positive for HPV 16/18/“Other” (across both study sites and both pathways) and who indicate on their consent form that they are happy to be contacted for an interview will be approached by a *wāhine* Māori researcher. They are invited to take part in an interview at a time and location that suits them and are encouraged to bring any *whānau* (family) or other support. During the interview, they are provided a *koha* (gift) as a small token of appreciation for sharing their experiences and perspectives. Key informants from primary care (eg, clinical staff, nonclinical staff, and management), colposcopy services (eg, clinical and nonclinical staff, and management), and the wider community are invited to be interviewed, either individually or in small groups. Most interviews are conducted in person, but some may be conducted by telephone or Zoom (Zoom Video Communications) depending on COVID-19 precautions and participant preferences [37]. Informed consent is obtained before the interview commences. The researcher takes time to follow culturally appropriate rituals of encounter that help to create a comfortable and safe environment for the interview [38]. Interviews are semistructured around 4 discussion points that aim to elicit rich, nuanced qualitative data. Participants are asked about the acceptability of the screening pathway, perceived level of empowerment and decision-making in the pathway, preferences for screening services, and recommendations for future screening programs. Participants are encouraged to add or ask anything else at the end of the interview. The interviews are audio recorded and transcribed verbatim.

All statistical analyses will be performed using SAS (version 9.4; SAS Institute) and R (version 3.4.2; R Foundation for Statistical Computing). Analyses will be intention to treat and conducted at the individual participant level. All tests of significance are 2-tailed and at a 5% significance level throughout the analyses. Continuous variables will be compared with *t* tests or Mann-Whitney *U* tests, and categorical data will be compared using chi-square tests, as appropriate.

A generalized linear regression model with a binomial distribution will be used to analyze binary outcomes, a linear regression model will be used to analyze continuous outcomes, and the cluster design will be taken into account in the analyses. For the primary outcome, both unadjusted and adjusted analyses for potential covariates measured at baseline will be conducted (eg, deprivation index and age). Unadjusted and adjusted odds ratios will be reported with corresponding 95% CIs and associated *P* values. Relative risks will also be estimated using Poisson regression models with robust error estimates. For the primary outcome, participants with missing data will be assumed as not having a colposcopy within 20 working days. Sensitivity analyses will be conducted for the primary outcome to assess the robustness of the results, which will include per-protocol analyses (where participants with any protocol deviations will be excluded). Additional sensitivity analyses may be considered, such as the potential impact of COVID-19 restrictions or extreme weather events. Subgroup analyses will be conducted for ethnicity, screening history, HPV type, and symptoms (if the numbers are sufficient). Time to notification and time to colposcopy will be analyzed using Kaplan-Meier curves, log-rank tests, and Cox proportional hazard models.

Qualitative data will be analyzed thematically. This will involve reading and rereading the transcripts, coding sections of data inductively, and combining and rearranging the codes to create themes and subthemes [39]. NVivo12 (QSR International) qualitative data analysis software will be used to assist in the coding and theming of data. In reporting the themes, feedback from participants will be written about in a way that groups their talk about common issues and how these issues are interrelated.

Importantly, the governance of this project rests with NPDT and NPO, giving community control of leading-edge POC technology. The study coordinating center is National Centre for Women’s Health Research Aotearoa and includes the roles of the principal investigator, project manager, investigators, research assistants, and Kaumātua. The study coordinating center is responsible for the day-to-day conduct of the trial and supports the practices to participate. This study is a multi-institutional, multidisciplinary, and international research collaboration. There are regular meetings once a week with the research team and once a month with the participating clinics. An external, independent data monitoring committee appointed by the Health Research Council of New Zealand was set up at the request of the research team and meets every 6 months to monitor safety and review recruitment progress and data completion. The National Centre for Women’s Health Research Aotearoa regularly meets the Ministry of Health National Screening Unit to update on the study progress and inform the new NCSP.

Harm to the participants in this trial is very unlikely. In that event, women are eligible to apply for compensation from the national Accident Compensation Corporation, just as if they were injured in an accident, at work, or at home. This study uses the national Health and Disability Ethics Committee’s (HDEC) definitions for serious adverse events, protocol deviations, and protocol violations. Events meeting these definitions are reported to the data monitoring committee and HDEC, along with the actions taken in response to any event.

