Most cervical cancers occur in women who have not undergone screening or are screened less frequently [10]. The National Cervical Screening Program (NCSP) shows that the target level of 80% of *wāhine* Māori screened within the previous 3 years is not achieved in any region; once screened, there is a failure to achieve a timely diagnosis and treatment of abnormalities for *wāhine* Māori [9]. Fewer *wāhine* Māori have a colposcopy within an appropriate time frame following a high-grade abnormality when compared with non-Māori women. Furthermore, the proportion of women who had no record of any subsequent follow-up at 90 days is 4.4% for European women but 8.6% for *wāhine* Māori [11].

The current national screening approach for cervical cytology involves an invasive procedure using a speculum, which requires attending a clinic with associated transport and other costs. Cervical screening in rural Aotearoa is performed by the primary care nurse or physician, and the tests are sent to a centralized laboratory for analysis. The results are returned to the primary care clinician, who then notifies the patient. If the result is abnormal, the clinician writes a referral letter to a gynecologist requesting an appointment for a colposcopy. Hospital departments then control all further investigations and treatments. Delays can occur at each point, which in turn create barriers to access, timely diagnosis, and treatment [12].

Human papillomavirus (HPV) is the causative agent of cervical cancer. Infection with certain oncogenic (cancer forming) high-risk types of HPV cause changes in the cells of the cervix that can lead to cancer. Compared with cytology, HPV-based screening is a better test; it provides 60% to 70% greater protection against developing invasive cervical cancers [13,14]. The World Health Organization recommends that all countries transition to HPV testing as the primary method for cervical screening [15-17]. It is also internationally recognized that a self-taken swab that uses molecular amplification testing platforms such as polymerase chain reaction is as effective in detecting high-risk HPV (hrHPV) as a clinician-taken sample [18,19].

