### Outcomes

The primary outcome is the proportion of women having a colposcopy within 20 working days from the test, for those women with a positive test result for hrHPV.

Secondary outcomes are of those with a positive hrHPV test result:

Proportion of women having a colposcopy within 40 working days of the testProportion of women having a colposcopy within 20 working days of referralProportion of women having a colposcopy within 40 working days of referralTime from test to colposcopyTime from referral to colposcopyNumber of high-grade lesions (cervical intraepithelial neoplasia and carcinoma)Planned treatment for women with high-grade histology at colposcopy.

Secondary outcomes include of all women taking the HPV test:

The proportion of women who test positive for hrHPVThe proportion of women who test negative for hrHPVThe proportion of women who have invalid resultsThe proportions due for screening, underscreened, or never screened.

Qualitative outcomes are as follows:

To explore and understand the successes and challenges of both pathways from the perspectives of the governance groups, clinical staff (nurses, doctors, *kaiāwhina* [nonclinical community health workers], and specialists), and women (including *whanau* or family supporters) at both sitesTo understand this new screening pathway to advise and inform a more culturally responsive NCSP.

On the basis of the percentage reported for *wāhine* Māori throughout Aotearoa, we estimated that 56.4% of women in the control arm will have a colposcopy within 20 working days following referral for a positive HPV test [30]. We aim to detect a 50% increase (relative risk 1.5) from 56.4% to 84% in the primary outcome for the intervention arm. A sample size of 80 women (n=40, 50% in each arm) in a 2-period, 2-cluster randomized crossover trial will provide 80% power at 2-sided α of .05 to detect a 50% increase in the intervention arm. With only 2 practices serving as the clusters, the sample size does not account for the cluster effect, which will be considered as a fixed effect in the final analysis.

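### The safety check at 3 months or later spares the primary outcome, but it can create successes in the two from-referral proportions and events in the open-ended time-to-colposcopy analyses

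*Protocol article*

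**What the plan says.** Under Data Collection and Analysis, the protocol article says that for clinical safety "the unblinded study statistician checks for colposcopy referrals and attendance". On timing: "This is checked no sooner than 3 months from the hrHPV test date". The stated purpose is "so the primary outcome is not influenced but ensures that practices can contact any woman who has not yet attended a colposcopy appointment". The assurance is given for the primary outcome only.

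Under Outcomes, "The primary outcome is the proportion of women having a colposcopy within 20 working days from the test", among women with a positive hrHPV result. The secondary outcomes for the same women are colposcopy within 40 working days of the test, colposcopy within 20 and within 40 working days of referral, time from test to colposcopy, and time from referral to colposcopy. Neither time has an upper limit.

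For analysis, "Time to notification and time to colposcopy will be analyzed using Kaplan-Meier curves, log-rank tests, and Cox proportional hazard models". The missing-data rule is also limited to the primary outcome: "For the primary outcome, participants with missing data will be assumed as not having a colposcopy within 20 working days".

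**The concern.** The check looks for missing referrals as well as missed visits, and it exists so that practices can act on what it finds. From that moment the trial can itself bring about a referral or an attendance. An outcome whose clock starts at the test and stops before the check is safe. An outcome whose clock starts at referral is not, because the check can start the clock. An outcome with no end date is not, because prompted visits are counted along with the rest.

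The article's first objective is timeliness, referral and attendance. Pathway 1 books colposcopy by phone straight away, while pathway 2 relies on a referral letter, triage and a mailed appointment. If missed referrals are commoner in pathway 2, the check would repair more of them there, and the secondary comparisons would understate the difference between the pathways.

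**Working it through.** **Inputs.** Check at 3 months or later; outcome windows of 20 and 40 working days; planning rates of 56.4% and 84%; 40 women per arm (Data Collection and Analysis; Outcomes). For scale only, the Introduction reports no recorded follow-up at 90 days for 8.6% of wāhine Māori and 4.4% of European women.

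**1. The plan's own figure.** The pooled two-proportion formula (two-sided 5%, 80% power, no continuity correction) gives 42 per arm for 56.4% against 84%. It gives 40 per arm for 56.4% against 84.6%, which is 1.5 × 56.4%. The stated 40 per arm is reproduced closely. The present point does not depend on it.

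**2. Windows against the check date.** 20 working days = 4 weeks = 28 calendar days. 40 working days = 8 weeks = 56 calendar days. 3 months = 365.25 / 4 = 91.3 days. Public holidays are ignored.

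| Outcome | Window closes | Can this check change it? |
|---|---|---|
| 20 working days from test (primary) | day 28 | No |
| 40 working days from test | day 56 | No |
| 20 working days from referral | referral day + 28 | Yes, if referred after about day 63 (91.3 − 28) |
| 40 working days from referral | referral day + 56 | Yes, if referred after about day 35 (91.3 − 56) |
| Time from test, time from referral | no limit stated | Yes, for visits after about day 91 |

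**3. Who is affected.** A woman referred promptly but unseen at 3 months has already failed both from-referral windows, and prompting cannot rescue her. The clear case is the woman with no referral by 3 months. The from-referral proportions are listed among all hrHPV-positive women, so until the check she is a non-success. Referred afterwards and seen within the window, she becomes a success, although she fails both from-test outcomes.

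**4. Size, under assumptions.** Let u be the share of control women first referred because of the check, and q the share of those seen within 20 working days of that referral. The control rate becomes 56.4% + u × q. The documents give neither u nor q. The two background percentages stand in for u, with q set at 56.4% or 100%.

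| u | q | Women of 40 | Control rate | Relative risk, control arm only affected | Relative risk, both arms equally affected |
|---|---|---|---|---|---|
| none | – | 0 | 56.4% | 1.49 | 1.49 |
| 4.4% | 56.4% | 1.0 | 58.9% | 1.43 | 1.47 |
| 4.4% | 100% | 1.8 | 60.8% | 1.38 | 1.45 |
| 8.6% | 56.4% | 1.9 | 61.3% | 1.37 | 1.45 |
| 8.6% | 100% | 3.4 | 65.0% | 1.29 | 1.42 |

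Bottom row: 0.086 × 40 = 3.4 women; 56.4 + 8.6 = 65.0; 84 / 65.0 = 1.29; both arms, (84 + 8.6) / 65.0 = 1.42. When both arms gain equally, the absolute difference stays at 84 − 56.4 = 27.6 points.

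**The case against.** The strongest reply is that the from-referral outcomes are meant to describe the step from referral to colposcopy, and that a missed referral is already penalised by the two from-test outcomes. That is fair as far as it goes: no missed referral escapes the trial's main measure. It does not explain why a referral made because of the trial's own check should count as pathway performance on the referral step.

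A second reply is that censoring dates belong in a statistical analysis plan, which is not shown. The absence of a censoring date is indeed no fault. What the article does fix is a prompt for missing referrals alongside outcomes that start at referral or never close, and it considers the effect on the primary outcome only.

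Three stronger readings are tempting, and the documents do not support them.

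- A reader might infer that every referral or attendance after 3 months is the trial's doing. Practices keep primary responsibility for follow-up, the check happens no sooner than 3 months, and it only enables contact. Late visits will include slow ordinary care.
- A reader might infer from "a linear regression model will be used to analyze continuous outcomes" that the two times will be analysed by linear regression, dropping women never seen. That is a general sentence; the survival methods are named specifically for time to colposcopy.
- A reader might take the 54 positives in the Results as a control count. They are the period 1 positives in both pathways together (54/743).

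The 8.6% is also not a non-referral rate after a positive self-test. It measures absence of any recorded follow-up, and the article gives it alongside colposcopy after a high-grade abnormality.

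**Conclusion.** The point holds for four secondary outcomes: the two from-referral proportions and the two times to colposcopy. It does not touch the primary outcome or the 40-working-days-from-test outcome. In time from test, a prompted visit still carries a long time, so only the part of the comparison after about day 91 is affected.

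Bias towards no difference is conditional. It needs more missed referrals in standard care, which the trial's hypothesis makes plausible but the documents do not show; the check applies to both pathways. The size is unknown. The rise from 56.4% to about 65% is an assumed upper bound that takes all 8.6% as unreferred and all of them as then seen promptly. Lower assumptions in the table give rises of about 2.5 to 5 points. Severity is minor: secondary outcomes, probably few women, and a cheap remedy.

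**What to change.** Change the analysis wording only.

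- **From-referral proportions (20 and 40 working days).** Keep all hrHPV-positive women in the denominator, and count as a non-success any woman with no referral within 3 months of her test.
- **Time to colposcopy.** End the main Kaplan-Meier, log-rank and Cox analyses at 3 months from the test in both pathways by administrative censoring. Report full follow-up as a sensitivity analysis.

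The safety check is unchanged and no new data are needed. The cost is that some genuine, unprompted attendances after 3 months leave the main time analysis; the sensitivity analysis still shows them. On the referral clock, women referred late will have short follow-up. A small gap also remains: a woman referred late but before 3 months (after about day 35 or day 63, depending on the window) could still be seen in time because of the prompt. Reporting the number of such women by pathway would show whether this matters.

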## Methods

### Overview

This is a cluster randomized crossover trial, with 2 primary care health practices (study sites) as clusters. Each site was randomized to implement either pathway 1 or pathway 2 in the first study period (15 months) and then crossing over to implement the other pathway in the second study period (15 months). The trial design is summarized in Figure 1.

Pathway 1 is HPV self-testing and POC results within 1 hour, with face-to-face information, support, and immediate referral to colposcopy for women with a positive test result for hrHPV—the community-controlled pathway.

Pathway 2 is HPV self-testing and laboratory analysis, followed by usual results giving, information and support, and standard referral pathways for women with a positive test result for hrHPV—the current standard pathway.

We hypothesize that pathway 1 will improve timely access to colposcopy compared with pathway 2.

We hypothesize that community control of the care pathways is acceptable and feasible for rural Māori communities.

This study is informed by the Kaupapa Māori inquiry paradigm. This paradigm sees being Māori as normal and challenges how Māori have been, and continue to be, constructed within a colonized worldview. It promotes a structural analysis of inequities for Māori, seeking to more fully understand people’s lives and the systemic determinants of their health and wellness [27,28]. In this paradigm, Māori worldviews, ways of knowing, and *mātauranga* Māori (Māori knowledge) are seen as valid and legitimate.

Non-Māori colleagues working collaboratively in a strengths-based approach are included in the team, which is Māori led [29]. With this Māori-centered approach led by *Kaumātua* (Māori elders and knowledge holders), we seek to combine multiple ways of knowing and seeing the world. Māori are involved at all levels, including protocol development, instigation, follow-up, and trialing of this innovative clinical care pathway [25]. Research practices reflect *tikanga* Māori (Māori customs), including the importance of place, relationships, and Māori self-determination [26,27].

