### Strength and Limitations

The strengths of this study include that it is informed by a Kaupapa Māori inquiry paradigm. This study was a collaboration between community, Iwi (tribes), rural primary health care clinicians; secondary care gynecology services; and the research team. Health care workers were trained to use POC technology and supported with regular quality assurance. This will lead to the possibility of testing for and treating other common infections in remote or environmentally isolated regions.

The limitations of this study include the recruitment for this study during COVID-19 disruptions and lockdowns and severe flooding and damage to infrastructure due to Cyclone Gabrielle, which affected both research sites. There was a difference in the research sites, as one site had 1 large rural clinic and the other site had 5 small rural clinics; however, there will still be the ability for the analysis to compare each site with itself on each pathway.

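### Site is the only design term named for a two-site, two-period crossover; period should be named with it, because a calendar-time effect leaks into the pathway estimate when the sites are unequal

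*Protocol article*

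**What the plan says.** The Overview section states: "This is a cluster randomized crossover trial, with 2 primary care health practices (study sites) as clusters". Each practice runs one pathway for 15 months and then the other.

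The sample-size paragraph of the Outcomes section explains that the calculation makes no allowance for "the cluster effect, which will be considered as a fixed effect in the final analysis". Data Collection and Analysis specifies binomial and linear regression and adds that "the cluster design will be taken into account in the analyses". The example covariates there are deprivation index and age. The same section lists t tests, Mann-Whitney and chi-square tests to be used as appropriate, then log-rank tests and Cox models for the time outcomes. It does not say whether these carry site or period. A sensitivity analysis for COVID-19 restrictions or extreme weather is mentioned as optional, with no method.

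Strength and Limitations reports COVID-19 disruption and "severe flooding and damage to infrastructure due to Cyclone Gabrielle, which affected both research sites". It then notes that one site has one large clinic and the other five small ones, and answers that "there will still be the ability for the analysis to compare each site with itself on each pathway".

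Period does not appear as a term in any model or test in the article.

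**The concern.** With two sites and two periods, pathway is the site-by-period contrast. Within one site, pathway 1 against pathway 2 is also one calendar period against the other. A site term removes stable differences between the practices but does nothing about calendar time. The crossover protects against a period effect shared by both sites because that effect enters with opposite signs at the two sites. With site alone in the model, the two signs cancel only if the sites carry equal weight. With period in the model as well, they cancel whatever the weights.

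Colposcopy within 20 working days is an outcome that lockdowns and damaged roads could plausibly change. If part of such a change were read as a pathway effect, the result meant to inform the national screening programme would be off by that amount, in either direction.

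**Working it through.** **The plan's own figure.** The target is "We aim to detect a 50% increase (relative risk 1.5) from 56.4% to 84% in the primary outcome for the intervention arm", with 40 women per arm. The exact relative risk of 1.5 gives 84.6%. A two-sided 5% comparison of 56.4% with 84.6% (pooled variance, no continuity correction) needs 40 per arm, with power 80.1%. At the rounded 84%, power with 40 per arm is 78.1%. The stated 80 women reproduces and is not in dispute.

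**Bias formula.** Call X the site that starts with pathway 1 and Y the other; the article does not say which is which. Let t be the pathway effect and d a period effect (period 2 minus period 1) common to both sites, both as risk differences.

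- Site X, pathway 1 minus pathway 2: t − d
- Site Y, pathway 1 minus pathway 2: t + d
- Information weight of a site: w = n1·n2/(n1 + n2), where n1 and n2 are its positives in each period
- Site-only estimate: t + d·(wY − wX)/(wX + wY)
- Site-plus-period estimate: the simple mean of the two contrasts, which is t

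**Leaked share |wY − wX|/(wX + wY).**

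| Positives at the two sites | Share of d that leaks | Bias at a 15-point shift |
|---|---|---|
| 27 and 27, each period | 0 | 0 |
| 34 and 20, each period | 14/54 = 26% | 3.9 points |
| 40 and 14, each period | 26/54 = 48% | 7.2 points |
| 27 and 27, then 8 and 18 | 27% | 4.1 points |

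The crude two-group contrast behind a chi-square test leaks a similar share. Its factor is nY2/(nX1 + nY2) − nX2/(nX2 + nY1), which is also 26% for 34 and 20 in each period.

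**How likely is such imbalance?** The Results section gives 370 and 373 tests in period 1 (one site each) and 54 positives in 743 (7.3%). Assume both periods look like that, with equal positivity at the two sites. Binomial simulation of the four cells then gives a leaked share with median about 6% and 95th percentile 19%. A share of 26% or more occurs in about 0.8% of trials. A 34/20 split in both periods is 68 against 40 overall (two-sided p = 0.009 under equality). A 40/14 split in both periods is 80 against 28 (p about 6 in 10 million).

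**Type I error.** Null trials were simulated with a 56.4% base rate, the period shift split evenly around it, and a Wald test for pathway in a logistic model. The shifts are assumptions; the article gives none.

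| Cells (same split in both periods) | Site only, 15 points | Site only, 25 points |
|---|---|---|
| 27/27 | about 4% | about 4% |
| 34/20 | about 6–7% | about 8–9% |
| 40/14 | about 10–11% | about 22–24% |

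Site plus period stayed at about 3–5%. Averaged over the chance imbalance above, the site-only model gave 5.3% (15 points) and 4.1% (25 points), which is nominal.

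**Cost of the period term.** With nX and nY positives per period, the variance ratio on the risk-difference scale is (nX + nY)²/(4·nX·nY).

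- Equal sites: 1.00
- 34/20: 2916/2720 = 1.07
- 3:1: 16/12 = 1.33

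In simulated logistic models with 80 women and cells of 30/30/10/10, power falls from about 77% to 47%. Part of that fall comes from small cells in a saturated model: a cell of 10 at 84% has complete attendance with probability 0.84^10 = 17%, and the Wald test then fails. For the same reason, simulated power at 20 per cell fell from 77.5% to 71.0% (0.84^20 = 3% per cell), although the variance ratio is 1.

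**The case against.** The strongest reply is that this is a condensed journal article. Model terms are commonly left to the full protocol or a statistical analysis plan, and the phrase about the cluster design is broad enough to include period. The site fixed effect is mentioned to explain why the sample size has no cluster inflation, not as a full model. The Outcomes section also says that each practice is a comparator for the other, which is the between-site comparison that deals with common period effects. All of this stands. A reader might infer that the final model will omit period; the article does not show that.

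A reader might also infer that the trial's type I error is inflated. The documents do not support that either. Period 1 testing was almost equal, and chance imbalance leaves the error rate nominal. Material inflation needs a systematic site difference in positivity or in period 2 recruitment, together with a large period shift, and the article reports neither.

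Nor is silence on stratification a stated choice. The simple tests are qualified as used where appropriate, and a Cox model can carry covariates.

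Two things survive. The optional COVID-19 and weather sensitivity analysis does not protect the primary analysis, since it may not be done and has no method. And the sentence about comparing each site with itself, although written to answer the difference in clinic structure, offers reassurance that does not extend to calendar time.

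**Conclusion.** The point holds in a limited form. For a two-period crossover, the article names site and leaves period unnamed, and it relies on a within-site comparison that is also a comparison of periods. The possible bias is the difference in site information weights times a common period effect. It is zero with balanced sites and probably small here: about 6% of the period effect at the median and 19% at the 95th percentile, assuming that both periods and both sites resemble the reported period 1 testing. It becomes serious only with marked, recurring imbalance: at 40/14 in both periods, 48% leaks and type I error is roughly 10–22% for assumed shifts of 15–25 points. Whether the trial is anywhere near that cannot be judged, because the site split of the 54 positives and all period 2 counts are not given.

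A period term has a limit of its own. A disruption that hits one site harder in one period is a site-by-period effect. With two sites and two periods it is fully aliased with pathway, and no model can remove it.

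This is a worthwhile, inexpensive clarification, not a must-fix error.

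**What to change.** 1. In Data Collection and Analysis, name site and period as fixed effects, with pathway, in the primary binomial model, the robust Poisson model and the Cox model.
2. Label the crude chi-square and log-rank comparisons as descriptive, or adjust them for site and period.
3. Report the four site-by-period proportions for the primary outcome, with their denominators, so that readers can see the balance and any one-sided disruption.
4. Amend Strength and Limitations to say that within-site comparisons alone are confounded with period, and that a shock falling harder on one site cannot be separated from pathway even with a period term.
5. State in advance what is done if a cell has complete attendance, for example a Firth-type logistic model or a standardised risk difference.

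The cost is wording, plus some precision: none on the risk-difference scale if the sites are balanced, about 7% more variance at 34/20, and a substantial loss of power at 3:1. That last loss should be acknowledged, since it reflects how little an unbalanced two-site crossover can tell pathway from period.
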